#### **4. Patient Safety:**

This is a non-interventional study. In this study, only cervical/vaginal samples will be collected. The occurrence of AEs / SAEs will therefore be considered unrelated to the diagnostic tests. Therefore, no indirect harm related to the investigated diagnostic tests is anticipated in the context of this study.

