In addition at the time of the physician visit (after the self-collection), the physician will obtain 2 “pseudo self-sample” specimens (prior to placement of a speculum). These 2 samples will be kept as “dry brush samples” by placing them in plastic bags and analyzed  $\leq 7$  days and  $> 6$  wks, respectively. (45)

As mentioned above, the major problem with primary HPV testing is specificity, since most of the women testing positive will have non-neoplastic HPV infections that will spontaneously clear. To address this issue we have previously investigated primary HPV screening with a mRNA assay. (46) In addition we have explored the use of 16/18 genotyping as well as multiple other HPV types for secondary triage after primary screening using both the Cervista assay and MALDI-TOF MS. (47,48) This current trial will provide the opportunity to expand that work applied to self-collection, the Cobas assay (tests for 16 and 18 separately), and SeqHPV with separate gene sequencing for 14 HPV High-risk types.

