### **3. Study Design**

#### **3.1 Methods**

This is a multicenter population-based cross-sectional cervical cancer-screening study that will provide screening for 10,000 women who have not been screened for cervical cancer in the past 3 years. The project will be submitted to the Peking University Shenzhen Hospital institutional review board and the IRB of the Cleveland Clinic in Cleveland, Ohio, USA for study approval. In addition the study will be registered with the Chinese Clinic Trial Registry, an international clinical trials registry platform approved by the WHO.

The clinical study consists of 1 self-sampling and 1 direct-sampling on all participants and 2 pseudo-self-sampling on participants in a high risk subset, all the samples will be used for multiple assays followed by referral for colposcopy and biopsy of women with positive test results from self-collection (any one assay), liquid direct collection (any one assay), plus pseudo-self-collection.

- 1) Recruitment of 10,000 patients for screening and participation in the study (Addendum flow chart)
  - Eligibility Criteria: non-pregnant, 30-59 yrs. of age, no screening for at least 3 years, no prior hysterectomy, no prior radiation, and willing to return for positive management if indicated by the primary tests.
  - Exclusion Criteria: Pregnant,  $< 30$  and  $> 59$  yrs of age, screening in the previous 3 years, history of a hysterectomy, pelvic radiation therapy, or not willing to return for positive management if indicated by the primary tests.
- 2) Informed consent

- 3) Demographics
- 4) Patient obtains 1 self-sample placed on the solid media transport card and then the brush (used as a split sample) placed and agitated in PreservCyt Liquid. The card sample will be obtained using the validated “Just for Me”™ kit, which includes a POI brush designed for both self and direct collection, a solid media specimen transport card (POI Card), and an envelope, all bar coded and contained within an outer envelope with language specific and pictorial sampling instructions. The PreservCyt sample will use the same POI brush and the sample will be placed directly into a vial containing 6ml PreservCyt.

- # 1 sample is first rubbed on the POI Card, then the brush agitated in a 6ml PreservCyt (TCT) (the split-sample).

These self-samples transported by card and liquid will be assayed using a) Roche-Cobas 4800 and b) BGI-SeqHPV test.

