### Assay:

- From the ❶ POI Card -----All SeqHPV (5ul HPV DNA); *nested* Cobas (10ul HPV DNA)
- From the ❷ PreservCyt (6ml) -----Cobas (1ml), SeqHPV(1ml)
- From the ❸ Sample A (reconstituted) ---- Cobas (1ml), SeqHPV (1ml)
- From the ❸ Sample B (reconstituted) -----*nested* Cobas (1ml), SeqHPV (1ml)
- From the ❹ PreservCyt(20ml)-----Cobas (1ml), SeqHPV(1ml), and Cytology.

- 6) Patients testing hrHPV positive from any of ❶ - to ❹ will be recalled for colposcopy using the POI protocol of directed and/or random biopsies plus ECC (49).
- 7) Patient management will be determined based on biopsy results and according to current standards at the Peking University Shenzhen Hospital.

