McNemars p-values for the comparison of the sensitivity of self-collected MALDI-TOF to physician collected Cervista is 1.0. McNemars p-value for the comparison for the specificities is  $p < 0.0001$

| SPECIMEN/HR-HPV TEST        | SENSITIVITY FOR <math>\geq</math>CIN 3 (%) (C.I.)(n) | SPECIFICITY FOR <math>\geq</math>CIN 3 (%) (C.I.)(n) |
|------------------------------------|-------------------------------------------------------------|-------------------------------------------------------------|
| Vaginal self-collected / Cervista  | 70.9% (62.7-78.3) (100/141)                          | 86.1% (85.3-86.8) (7248/8415)                        |
| Endocervical / Cervista            | 95.0% (90.0-98.0) (134/141)                          | 90.3% (89.6-90.9) (7598/8415)                        |
| Vaginal self-collected / MALDI-TOF | 94.3% (89.1-97.5) (133/141)                          | 87.5% (86.8-88.2) (7370/8415)                        |
| Endocervical / MALDI-TOF           | 94.3% (89.1-97.5) (133/141)                          | 89.4% (88.7-90.0) (7526/8415)                        |

The 95% CI for the sensitivity of hrHPV in Table 1 spans about 8%, suggesting that, with a study involving 10,000 women with prevalence of hrHPV of 11.1 to 14.8% and prevalence of CIN 3+ of 1.6%, we can reliably detect a difference in sensitivity of about 8%. The 95% CI for the specificity of hrHPV in Table 1 spans only about 1.3% suggesting that we can reliably detect differences in specificity of the hrHPV test greater than 1.3%. As we have paired specimens, the difference in sensitivity for CIN 3+ that can reliably be detected is closer to 7% i.e. 94.3% (133/141) vs. 87.2% (123/141) rather than 8%.

*Primary Objective: Evaluation of the Cobas 4800 Assay, and the SeqHPV Assay for the detection of high grade pre-cancer of the uterine cervix, in population based screening samples obtained using self-collection.*

To evaluate the comparative sensitivities and specificities of the hrHPV platforms, the sensitivity and specificity of each test will be calculated using biopsy showing CIN 3+ (primary endpoint) or CIN 2+ (secondary endpoint) as the gold standards.

*Secondary objective 1: To evaluate differences in assay performance using solid (filter paper cards), dry brush, and liquid based specimen transport for the self-collected and physician collected cervico-vaginal specimens.*

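### Section 4 expects no indirect harm from the tests, although a positive test sends a woman to protocol-specified colposcopy, biopsy and ECC

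*Protocol*

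**What the plan says.** Section 4 is one short paragraph. It classes the study as non-interventional and gives as its premise: "In this study, only cervical/vaginal samples will be collected". From this it draws two conclusions. The first concerns causality: "The occurrence of AEs / SAEs will therefore be considered unrelated to the diagnostic tests". The second concerns harm: "Therefore, no indirect harm related to the investigated diagnostic tests is anticipated in the context of this study". Colposcopy, biopsy, ECC and false-positive results are not mentioned.

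Other parts of the protocol prescribe what follows a positive test:

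- Section 3.1, item 6 (after the assay list): women who are hrHPV positive on any of the four sample types "will be recalled for colposcopy using the POI protocol of directed and/or random biopsies plus ECC". The overview at the start of section 3.1 counts this referral as part of the clinical study.
- Section 3.1, eligibility: participants must be "willing to return for positive management if indicated by the primary tests".
- Section 3.3, Statistical Methods: sensitivity and specificity are calculated "using biopsy showing CIN 3+ (primary endpoint) or CIN 2+ (secondary endpoint) as the gold standards".
- Section 2, on the limited specificity of primary HPV testing: "since most of the women testing positive will have non-neoplastic HPV infections that will spontaneously clear".

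**The concern.** The ordinary meaning of indirect harm from a diagnostic test is harm from what is done because of its result. Item 6 of section 3.1 creates exactly that pathway: a positive study assay leads to a biopsy procedure that the protocol itself specifies. Section 4 reasons from specimen collection alone and then makes a statement that also covers the consequences of the result.

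The causality sentence adds to the problem. It settles the relation to the tests before any event has been seen, and it does not separate sampling and assay from the recall they trigger.

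What is at stake is how safety is stated and assessed. The most invasive procedures in the protocol are missing from its safety section, and a committee reading section 4 alone would not learn of them there. By the protocol's own account, most women exposed to them will have infections that clear.

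**Working it through.** **Step 1. The texts side by side.**

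| Question | Section 4 | Sections 3.1 and 3.3 |
|---|---|---|
| What is done to participants? | Cervical and vaginal sampling | Sampling, then colposcopy, biopsy and ECC for test-positive women |
| What triggers it? | Not addressed | A positive hrHPV result on any study sample |
| Is it study procedure or local care? | Not addressed | Biopsy method fixed in item 6; biopsy is the reference standard; only management after biopsy (item 7) is left to hospital standards |
| Can a test lead to harm indirectly? | None anticipated | A pathway is prescribed |

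The last row does not depend on whether a biopsy counts as a cervical sample. If it does, the samples include tissue biopsies, and the step from samples only to no indirect harm is weaker still.

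**Step 2. Reproduce the planning figures.** Section 3.3 gives SHENCCAST II hrHPV positivity of 11.1% to 14.8% and CIN 3+ prevalence of 1.6%. Table 1 has 141 women with CIN 3+ and 8,415 without, 8,556 in all.

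- Prevalence: 141/8,556 = 1.6%, as stated.
- False positives (FP) = 8,415 − true negatives. Positives = true positives (TP) + FP.
- Share of positives without CIN 3+ = FP/positives.

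| Sample / assay | TP | FP | Positives (of 8,556) | Without CIN 3+ | FP per TP |
|---|---|---|---|---|---|
| Self / Cervista | 100 | 8,415 − 7,248 = 1,167 | 1,267 (14.8%) | 92.1% | 11.7 |
| Endocervical / Cervista | 134 | 8,415 − 7,598 = 817 | 951 (11.1%) | 85.9% | 6.1 |
| Self / MALDI-TOF | 133 | 8,415 − 7,370 = 1,045 | 1,178 (13.8%) | 88.7% | 7.9 |
| Endocervical / MALDI-TOF | 133 | 8,415 − 7,526 = 889 | 1,022 (11.9%) | 87.0% | 6.7 |

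The positivity range is reproduced.

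**Step 3. Scale to this trial** by 10,000/8,556, assuming that the rates carry over and every recalled woman attends.

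- Recalled on one test: 951 × 10,000/8,556 = 1,112 to 1,267 × 10,000/8,556 = 1,481.
- Of these, without CIN 3+: 817 × 10,000/8,556 = 955 to 1,167 × 10,000/8,556 = 1,364.
- If only 80% attended (an assumption), 889 to 1,185 women would be examined.

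**Step 4. Allow for CIN 2.** Women without CIN 3+ include those with CIN 2, which counts towards the secondary endpoint. SHENCCAST II had 227 − 141 = 86 such women. Even if all 86 had tested positive, the share of positives without CIN 2+ would be (817 − 86)/951 = 76.9% for endocervical Cervista and (1,167 − 86)/1,267 = 85.3% for self-collected Cervista. The other two rows fall between, at 803/1,022 = 78.6% and 959/1,178 = 81.4%.

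**Step 5. Direction of error.** For a given set of tests on the same women, recall on any positive cannot be lower than recall on one of them. The 22% HPV rate that section 3.2 reports for the Inner Mongolia site also points upward. It is left out of the calculation because neither the assay nor a restriction to high-risk types is given, and the number of women per site is not stated. Because the assays and age range differ from SHENCCAST II, the Step 3 figures are not a strict lower bound.

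**The case against.** The best defence is that section 4 is narrow by intent. Its closing sentence is a forecast, limited to harm related to the investigated tests. The protocol does not define indirect harm, and the eligibility criterion treats the return visit as management of a positive result. On that reading, section 4 covers swab and assay only. This makes the wording less stark but does not rescue it. The biopsy procedure is fixed by the protocol and supplies the endpoint, so it is not simply local follow-up, and the word indirect reaches beyond swab and assay.

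Several stronger readings are tempting, and the document does not support them:

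- *The premise is false.* Biopsies and ECC can be read as cervical samples. The premise is incomplete, not untrue.
- *Adverse events will go unrecorded, or none can be attributed to a biopsy.* The causality sentence concerns the tests only. It neither waives recording nor bars attribution to a procedure.
- *Women are not told of the risks.* Section 5 requires oral and written information on procedures and potential risks, under the Declaration of Helsinki and ICH GCP, and section 3.1 names the procedures openly. The consent pages are not in the review copy, so nothing can be inferred about their content.

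Section 5 is general, however, and does not correct section 4. It is also fair to say that the figures above measure exposure and not the defect itself.

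**Conclusion.** The concern holds as a wrong statement in the safety section. Section 4 judges adverse events unrelated to the tests in advance and anticipates no indirect harm, while section 3.1 makes colposcopy, biopsy and ECC the prescribed consequence of a positive test. Complications of that work-up are therefore foreseeable.

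The size is about 1,110 to 1,480 recalled women per 10,000 for a single test, with about 86% to 92% of them free of CIN 3+. The counts assume that SHENCCAST II positivity (other assays, ages 25 to 59) carries over and that all recalled women attend. The percentages assume that accuracy and prevalence carry over and that attendance does not depend on disease status.

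A reader might take these figures as numbers of women harmed, or take the percentages as women without any high-grade lesion. Neither is supported: the protocol gives no complication rate, and some of these women would have CIN 2. Nor does the point bear on the accuracy results. It should be corrected because it affects how safety is described and assessed.

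**What to change.** In section 4:

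1. Name colposcopy, biopsy (directed, random or both) and ECC as protocol procedures prompted by a positive test.
2. Delete the closing sentence on indirect harm.
3. Limit the advance statement on causality to sample collection and the assays, with case-by-case causality assessment for events after recall procedures.
4. Record such events by exception at the recall visit. Section 3.3 describes the study forms only for questionnaire and laboratory data, so add an adverse event field if none exists.

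The cost is a few sentences, a small form change and recording only when an event is seen or reported. An ethics amendment is probably needed, since section 5 requires written approval of changes that call for ethical consideration and section 3.1 names two review boards. No contact after the recall visit is added, so delayed events that a woman does not report would still be missed. Endpoints, sample size and accuracy analyses do not change.

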#### **5. Compliance Statement:**

Study approval by the IRBs of the Cleveland Clinic and Peking University Shenzhen Hospital meets all of the elements covered by the following compliance statement:

*The study will be conducted in compliance to this study protocol, the current version of the Declaration of Helsinki, ICH GCP, and applicable local legal and regulatory requirements.*

*Submission of study documents: Before study start, the study protocol, and subject information / informed consent and any other study-related document as required by applicable laws and regulations will be submitted to the Ethics Committee and regulatory authorities for written approval. Any protocol amendments or new or amended information that requires ethical consideration will be submitted for written approval, too. In addition, a study report (interim and /or full report) will be submitted to regulatory authorities in line with applicable timelines.*

*Subject information and informed consent: Subjects/legal representatives will be informed orally and in writing about the objectives of the study, study procedures, potential risks, and about the fact that to some extent data will be accessible for third parties (see below) for the purpose of controlling the study conduct - provided that data confidentiality is ensured at any time.*

*Before any study-related activities are initiated, the subjects / legal representatives will have to sign the written informed consent. The participation in the study is entirely voluntary. The subjects have the right to withdraw their willingness to participate in the study at any time without affecting their future medical care in any way.*

*Clinical study results and publication: The results of the clinical study will be documented in a clinical study report and if possible, will be published (e.g. in a journal or presented in a scientific meeting).*

